### Ethics

This clinical investigation will be conducted in accordance with the ethical principles that have their origin in the Declaration of Helsinki. This clinical investigation will comply with the practices set out in EN ISO14155:2011. This investigation was approved by the Medical Ethics Committee of the Leiden University Medical Center (NL61603.058.18). The study will be conducted according to the rules on medical research involving human subjects (Medical Research (Human Subjects) Act), in Dutch: Wet Medisch-Wetenschappelijk Onderzoek met mensen (WMO). In addition, approval has been obtained from all of the participating hospitals: Amsterdam University Medical Center (Amsterdam Medical Center and Vrije Universiteit University Medical Center), University Medical Center Utrecht, Erasmus medical Center, IJsselland hospital, Alrijne hospital, Haaglanden Medical Center, Diakonessenhuis, Deventer hospital, Meander Medical Center and the St. Antonius hospital.

### Data-analysis

To assess the non-inferiority of the ESD procedure, the difference between the cumulative recurrence rates at 12 months in both groups will be compared to the non-inferiority margin of 3% using a one-sided Mantel-Haenszel test (with alpha 0.025) to account for stratification factors. For the other variables, normality will firstly be assessed. The secondary endpoints will be compared using the student t-test or Mann-Whitney U test and Chi-square or Fisher’s exact test as appropriate. Multivariate regression will be considered for adjustment for possible confounding if necessary. The analysis will primarily be carried out on an intention-to-treat basis.

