**Methods:**

Multicenter randomised trial in 15 hospitals in the Netherlands. Patients with non-pedunculated lesions > 2 cm, where the bulk of the lesion is below 15 cm from the anal verge, will be randomised between either a TAMIS or an ESD procedure. Lesions judged to be deeply invasive by an expert panel will be excluded. The primary endpoint is the cumulative local recurrence rate at follow-up rectoscopy at 12 months. Secondary endpoints are: 1) Radical (R0-) resection rate; 2) Perceived burden and quality of life; 3) Cost effectiveness at 12 months; 4) Surgical referral rate at 12 months; 5) Complication rate; 6) Local recurrence rate at 6 months. For this non-inferiority trial, the total sample size of 198 is based on an expected local recurrence rate of 3% in the ESD group, 6% in the TAMIS group and considering a difference of less than 6% to be non-inferior.

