### Sample size calculation

The sample size was calculated for the primary outcome parameter, the cumulative recurrence rate at 12 months. To assess the non-inferiority of the ESD procedure the sample size calculation was based on the assumption that the recurrence rate will be 3% in the ESD group and 6% in the TAMIS group based on a systematic review of the literature specifically for studies performed in the West. If there is a true difference in favour of ESD of 3%, then 166 patients are required to be 80% sure that the upper limit of a one-sided 97.5% confidence interval (or equivalently a 95% two-sided confidence interval) will exclude a difference in favour of the TAMIS of more than 6%. (Software: PASS Version 15 – www.ncss.com). We have chosen a non-inferiority margin of 6% because we believe that this difference in risk of benign recurrence between the intervention group and usual care group is clinically acceptable. To allow for patients lost to follow-up (4%) and patients requiring additional surgical resection due to high risk characteristics (12%) in whom the primary outcome cannot be assessed, a total of 198 patients will be included; 99 patients in each arm. The incidence of large rectal non-pedunculated lesions in the Netherlands is estimated to be between 250 and 500 new cases a year. We estimated that the participation of 15 centres will be required to complete the inclusion period within 3 years. To avoid unnecessary delay, we will start this trial with 5 centres and will extend the number of centres during the course of the trial.

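### The non-inferiority margin is 6% in the abstract and sample size section but 3% in the planned analysis; if the 3% is applied as written, power is about 46%, not 80%

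*Protocol article*

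**What the plan says.** All three statements are in the protocol article and concern non-inferiority of ESD to TAMIS on local recurrence at 12 months.

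- **Abstract, Methods:** the total of 198 is based on expected rates of 3% (ESD) and 6% (TAMIS), "considering a difference of less than 6% to be non-inferior".
- **Sample size calculation:** the planning assumption is that "the recurrence rate will be 3% in the ESD group and 6% in the TAMIS group". On that basis "166 patients are required to be 80% sure" that the upper confidence limit, at one-sided 97.5%, "will exclude a difference in favour of the TAMIS of more than 6" per cent. The choice is then justified on clinical grounds: "We have chosen a non-inferiority margin of 6% because we believe that this difference in risk of benign recurrence" is acceptable.
- **Data-analysis:** the difference in cumulative recurrence "will be compared to the non-inferiority margin of 3" per cent, with a one-sided Mantel-Haenszel test at alpha 0.025 that accounts for the stratification factors.

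The article neither explains the change from 6% to 3% nor says which section takes precedence.

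**The concern.** The margin is the success criterion for the primary endpoint, and the article states it in two incompatible ways. Any result with an upper confidence limit between 3 and 6 percentage points is non-inferior by the abstract and sample size section, and not non-inferior by the analysis section.

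Two things are at stake. First, the 80% power claim belongs to the 6% rule, while the sentence that defines the test uses 3%. Second, the trial is unblinded. If the discrepancy is noticed only once recurrences by arm are known, it would be hard to show that the choice of margin was independent of the data, and the nominal one-sided 2.5% error rate could no longer be claimed with confidence.

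**Working it through.** **Inputs** (Sample size calculation section unless noted)
- Recurrence: ESD 3%, TAMIS 6%, so the true difference (ESD minus TAMIS) is −0.03.
- One-sided alpha 0.025 (z = 1.960); power 80% (z = 0.842).
- Not assessable: 4% lost to follow-up plus 12% additional surgery, 16% in all.
- Margin M: 0.06 (abstract, sample size section) or 0.03 (Data-analysis).

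**Step 1: reproduce the stated sample size.** With the unpooled normal approximation,

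n per arm = (1.960 + 0.842)² × (0.03×0.97 + 0.06×0.94) / (M + 0.03)².

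The variance term is 0.0291 + 0.0564 = 0.0855.

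- M = 0.06: denominator 0.09² = 0.0081, n = 82.85, rounded up to 83 per arm, 166 in total. Then 166 / 0.84 = 197.6, rounded up to 198. Both stated figures are matched exactly.
- M = 0.03: denominator 0.06² = 0.0036, n = 186.4, rounded up to 187 per arm, 374 in total. Then 374 / 0.84 = 445.2, rounded up to 446.

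**Step 2: power at the planned size.** Power = Φ[(M + 0.03) / √(0.0855/n) − 1.960]. At n = 83 the standard error is √(0.0855/83) = 0.0321.

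- M = 0.06: Φ(0.09/0.0321 − 1.960) = Φ(0.844) = 80.1%.
- M = 0.03: Φ(0.06/0.0321 − 1.960) = Φ(−0.091) = 46.4%.

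**Step 3: sensitivity to method and evaluable number.** The exact figures enumerate the two binomial distributions.

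| Evaluable per arm | Method | Power, 6% margin | Power, 3% margin |
|---|---|---|---|
| 83 | Normal approximation | 80.1% | 46.4% |
| 83 | Exact, Wald interval | 82.8% | 48.3% |
| 83 | Exact, Farrington-Manning score | 73.4% | 38.7% |
| 99 | Normal approximation | 86.5% | 53.3% |
| 99 | Exact, Wald interval | 87.4% | 56.8% |
| 99 | Exact, Farrington-Manning score | 80.9% | 49.0% |

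At 83 per arm the smaller margin costs about 34 to 35 points of power by every method. Even if all 99 per arm were evaluable, no method gets above 57% with a 3% margin.

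**Step 4: how often the two rules disagree.** Under the planning rates with 83 per arm and the Wald interval, the probability of passing at 6% but failing at 3% is 82.8% − 48.3% = 34.5%. Results close to plan fall in this zone:

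- 3/83 on ESD against 5/83 on TAMIS: difference −2.4 points, upper 95% limit −2.4 + 1.960 × 3.32 = 4.1 points.
- 3/83 against 3/83: difference 0, upper limit 1.960 × 2.90 = 5.7 points.

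Both pass at 6% and fail at 3%.

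**Step 5: error rate if 3% is meant but 6% is applied.** Take ESD truly 3 points worse, with rates of 9% and 6% chosen for illustration. Exact enumeration with the Wald interval declares non-inferiority in 12.6% of trials at the 6% margin, against 2.7% at the 3% margin.

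**The case against.** The strongest reply is that 6% is plainly what was meant. It appears in the abstract and twice in the sample size section, it is the only value with a clinical rationale, and the sample size is built on it. The 3% appears once, without a reason, and equals the assumed true difference. On that reading the trial is adequately powered and 46% describes a design nobody intended. This has force, and the power figure should be read as conditional on applying the Data-analysis section as written. It does not remove the contradiction, because the odd value stands in the one sentence that specifies the primary test.

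Three smaller points can be made. The full protocol is not shown and may fix a single margin; but the article states a figure that conflicts with itself, which differs from leaving a detail out. The loss of type I error control is a risk that arises only if the margin is settled late, and nothing in the article says it will be. The stratified Mantel-Haenszel analysis was not modelled; it could shift power slightly, but not from 46% to 80%.

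**Conclusion.** The concern holds. The article gives two margins, 6% and 3%, for the same endpoint, comparison and alpha, and does not reconcile them. The sample size supports only the 6% margin. Applied as written, the analysis section leaves about 46% power at 83 evaluable per arm (39% to 48% across the exact methods), and the two rules would give opposite conclusions in roughly one trial in three.

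These figures rest on the protocol's own assumptions: true rates of 3% and 6%, 16% not assessable, one-sided alpha 0.025, and an unstratified comparison of proportions. The contradiction itself rests on none of them. It must be corrected before outcomes are compared by arm.

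**What to change.** State one margin throughout, by dated amendment made before any comparison of recurrence by arm.

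- **If 6% is intended:** correct the figure in the Data-analysis section. State that non-inferiority is concluded when the upper limit of the two-sided 95% confidence interval for ESD minus TAMIS is below 6 percentage points, with the interval taken from the stratified Mantel-Haenszel estimate so that the planned adjustment is kept. This matches the criterion in the sample size section. It costs a change of wording and no extra patients.
- **If 3% is intended:** correct the abstract and sample size section, give a rationale for 3%, withdraw the 80% power claim and report about 46%. Restoring 80% under the same assumptions would take 374 evaluable patients, about 446 randomised instead of 198.

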### Randomisation

Patient data will be entered into a cloud-based electronic data capture system (Castor). This system will randomise patients to either the TAMIS or the ESD group. Stratification will take place for the distance of the lesion to the dentate line and lesion size.

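### The test named for the primary non-inferiority comparison has no margin term, and its nearest workable form does not hold the stated one-sided 0.025

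*Protocol article*

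**What the plan says.** Protocol article, Data-analysis: to assess non-inferiority of ESD, "the difference between the cumulative recurrence rates at 12 months in both groups will be compared to the non-inferiority margin of 3" per cent, and this is to be done "using a one-sided Mantel-Haenszel test (with alpha 0.025) to account for stratification factors". No estimator, variance or interval is given there.

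Protocol article, Sample size calculation: the trial is sized on a confidence-limit rule, that "the upper limit of a one-sided 97.5% confidence interval (or equivalently a 95% two-sided confidence interval) will exclude a difference" beyond the margin, and there "We have chosen a non-inferiority margin of 6" per cent. The assumption is that "the recurrence rate will be 3% in the ESD group and 6% in the TAMIS group", with 80% power and 166 evaluable patients. The Abstract also uses 6%.

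Protocol article, Randomisation: "Stratification will take place for the distance of the lesion to the dentate line and lesion size". The number of strata and their cut-points are not given.

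**The concern.** The Mantel-Haenszel test, as the name is ordinarily used, asks whether the stratum-adjusted odds ratio is 1. Its statistic compares observed with expected events under no association, so a risk-difference margin cannot enter it. The Data-analysis sentence therefore asks for one thing (a difference against a margin) and names a tool that delivers another. The Sample size calculation describes a third form, an upper confidence limit.

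An analyst has to reinterpret the named test before the trial's one confirmatory claim can be made. The obvious reinterpretation, a Mantel-Haenszel risk difference with its usual large-sample variance, rests on few events: at the design rates, 83 × 0.03 + 83 × 0.06 = 7.5 recurrences in total. At such counts the choice of variance affects whether the error rate stays at the stated 0.025.

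**Working it through.** **Inputs from the protocol.** ESD 3%, TAMIS 6%, margin 6% (Sample size calculation), one-sided alpha 0.025, power 80%, 166 evaluable, 198 in total after 4% + 12% = 16% attrition. **Assumed:** 4 or 6 equal strata, with risks either equal across strata or varying by multipliers from 0.4 to 1.6.

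**1. Reproduce the sample size.** Unpooled (Wald) formula per arm:

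n = (1.960 + 0.842)² × (0.03 × 0.97 + 0.06 × 0.94) / (0.06 + 0.03)² = 7.849 × 0.0855 / 0.0081 = 82.85, so 83 per arm and 166 in total. Then 166 / 0.84 = 197.6, so 198. Both stated figures are matched. The Farrington-Manning score formula gives 106 per arm (212), so the plan's figure is of Wald type.

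**2. Nearest workable reading of the named test.** Let RD be the Mantel-Haenszel-weighted difference, ESD minus TAMIS, with weights n₁n₂/(n₁+n₂) per stratum, and SE its Sato large-sample standard error. Reject inferiority if (RD − 0.06)/SE < −1.96. Type I error is evaluated where the true difference equals the margin. All rows use 83 per arm.

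| Method | 12% vs 6% | 9% vs 3% |
|---|---|---|
| Mantel-Haenszel RD, Sato variance (simulated, 4 or 6 strata) | about 3.2% | about 4.2% |
| Unstratified Wald (exact enumeration) | 3.0% | 4.2% |
| Unstratified Farrington-Manning score (exact enumeration) | 2.3% | 2.1% |
| Stratified score, Mantel-Haenszel weights (simulated, 4 or 6 strata) | 2.2-2.3% | 1.9-2.0% |

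The first two rows agree, so stratification is not the source of the excess. The score rows, stratified or not, stay below 2.5%. Expected recurrences at these boundary points are 83 × 0.18 = 14.9 and 83 × 0.12 = 10.0.

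**3. Power at 3% vs 6%, margin 6%, 83 per arm.** Wald formula 80%; Mantel-Haenszel RD with Sato variance 83% (simulated); unstratified score test 73% (exact); stratified score about 72% (simulated). With 99 evaluable per arm the unstratified score test reaches 81% (exact).

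**4. The literal routine, for reference.** A Cochran-Mantel-Haenszel test against no association, one-sided at 0.025, rejects in about 13-14% of trials at 3% vs 6%.

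**5. The margin in the same sentence.** With 3% in place of 6%, the formula in step 1 gives 187 per arm (374 evaluable), and Wald power at 83 per arm is 46%. Only 6% reproduces 166.

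**The case against.** A reader might infer that the trial, run as written, tests superiority of ESD with some 14% power. The protocol does not support that. The Data-analysis sentence opens with non-inferiority and ties the difference to a margin. The Design section and the primary endpoint heading say non-inferiority, and no section states a zero-difference null for the primary endpoint. The 13-14% figure belongs to a literal software routine that the rest of the sentence does not describe.

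It is also fair to say that Mantel-Haenszel methods can carry a margin: the weighted risk difference does so, and its power of about 83% is in line with the planned 80%. On this view only a variance formula is unnamed, and a condensed article may leave that to the analysis plan. The excess is moderate, too: at the planned TAMIS rate of 6% it is about 0.7 percentage points, and the larger figure assumes a TAMIS rate of 3%, half the planned one.

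Most of this stands and limits the point. What it does not remove is that the article positively names a test for its confirmatory claim, that the test in its standard form has no margin term, and that the reading needed to rescue it exceeds the error rate stated in the same sentence.

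**Conclusion.** The point holds as a mismatch between the stated comparison and the named method. It is not a claim that the trial tests the wrong hypothesis. In its nearest workable form the named analysis runs at about 3.2% (12% vs 6%) to 4.2% (9% vs 3%) against a stated 2.5%. These figures rest on 83 evaluable per arm, a 6% margin, 4 to 6 assumed strata and the Sato variance. They change little with the stratum layout, because plain Wald gives 3.0% and 4.2%.

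The 3% margin in Data-analysis contradicts the 6% in the Abstract and the Sample size calculation. That is a separate contradiction, but it sits in the sentence to be rewritten and has to be settled with it.

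**What to change.** Replace the named test in Data-analysis with: the primary estimate is the risk difference (ESD minus TAMIS) in 12-month cumulative recurrence, combined over the randomisation strata with Mantel-Haenszel weights, with a stratified Miettinen-Nurminen (score) two-sided 95% confidence interval; non-inferiority is concluded if the upper limit is below the margin. Add a rule for collapsing a stratum that has no patients in one arm. This agrees with the rule in the Sample size calculation. Before adopting it, reconcile the 3% and 6% margins across Data-analysis, the Abstract and the Sample size calculation.

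The edit is short, but it has a price. With a 6% margin and 166 evaluable patients, the stated 80% power should be restated as about 71-73%. Keeping 80% would need more evaluable patients: 99 per arm gives 81% by exact enumeration of the unstratified score test, and the score formula asks for 106 per arm. With 16% attrition that means 198 / 0.84 = 235.7 (236) or 212 / 0.84 = 252.4 (253) randomised, against the planned 198. The sponsor should either accept and report the lower power or revise the sample size.

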### Design

This will be a multicentre randomised non-inferiority trial comparing TAMIS and ESD in patients with large rectal lesions. The flowchart of the design of the TRIASSIC study is shown in Fig. 1.

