### Intervention failure: cross-over

If the primary procedure fails, cross-over to the other treatment is possible, but only if the specialist that has to perform the cross-over treatment, deems it feasible.

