### Outcomes

#### Primary study endpoint (for non-inferiority)

Cumulative recurrence rate at follow-up rectoscopy after 12 months, histologically confirmed from resected visible residual disease or, if not present, from biopsies of the scar

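### Non-inferiority is judged primarily by intention-to-treat although failed procedures may cross over to the comparator; if ESD is truly worse, this can modestly raise the false non-inferiority rate

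*Protocol article*

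**What the plan says.** The Design section sets the framework: "This will be a multicentre randomised non-inferiority trial comparing TAMIS and ESD in patients with large rectal lesions". The primary endpoint is binary: "Cumulative recurrence rate at follow-up rectoscopy after 12 months", confirmed by histology.

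Two stated choices meet here. Under Intervention failure: cross-over, "If the primary procedure fails, cross-over to the other treatment is possible", provided the specialist who would perform the second treatment considers it feasible. Under Data-analysis, "The analysis will primarily be carried out on an intention-to-treat basis".

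The test is described as "using a one-sided Mantel-Haenszel test (with alpha 0.025". The Hypothesis, Objective and Data-analysis sections all word the comparison as one between procedures. The Sample size calculation section adds patients for loss to follow-up (4%) and for additional surgery (12%), but makes no allowance for cross-over and gives no expected rate of it.

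**The concern.** In this trial the rescue treatment for a failed procedure is the comparator. Analysed as randomised, a patient whose ESD fails, who then has TAMIS and stays free of recurrence, is recorded as recurrence-free under ESD. The reverse holds for a failed TAMIS.

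In a superiority trial such mixing usually makes a positive claim harder to reach. In a non-inferiority trial it can make the claim easier, because mixing pulls the arms together and similarity is what the test rewards. At stake is whether a conclusion worded for the ESD procedure could rest partly on TAMIS having completed the difficult cases.

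**Working it through.** **Inputs from the protocol article.** Sample size calculation: "the recurrence rate will be 3% in the ESD group and 6% in the TAMIS group"; 80% power; one-sided 97.5% limit; 166 evaluable patients (83 per arm); 198 in total. The margin there reads "We have chosen a non-inferiority margin of 6" (percent), whereas Data-analysis has "compared to the non-inferiority margin of 3" (percent). That conflict is a separate matter, so both values are run here.

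**Step 1: reproduce the plan's own figure.** With the unpooled normal approximation,

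n per arm = (1.960 + 0.842)² × (0.03×0.97 + 0.06×0.94) / (0.06 + 0.03)² = 82.8, rounded up to 83, so 166 in total.

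Inflation: 166 / (1 − 0.16) = 197.6, so 198. Both figures reproduce. Power at 83 per arm is 80.1%.

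**Step 2: model of cross-over.** Let c1 be the proportion crossing from ESD to TAMIS and c2 the proportion crossing from TAMIS to ESD. Assume that crossed patients have the recurrence risk of the treatment received. Then

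- ESD arm as randomised: pE' = pE(1 − c1) + pT·c1
- TAMIS arm as randomised: pT' = pT(1 − c2) + pE·c2
- P(claim non-inferiority) = Φ((margin − (pE' − pT'))/SE − 1.96), where SE² = [pE'(1 − pE') + pT'(1 − pT')]/83

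This ignores stratification. The values of c1 and c2 are assumptions, since the documents give none.

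**Step 3: ESD truly worse by exactly the margin.** For the 6-point margin, TAMIS is 6% and ESD 12%. For the 3-point margin, TAMIS is 6% and ESD 9%.

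| c1 | c2 | Difference as randomised (6-point case) | False claim, 6-point margin | False claim, 3-point margin |
|---|---|---|---|---|
| 0 | 0 | 6.0 points | 2.5% | 2.5% |
| 2% | 2% | 5.76 | 2.8% | 2.7% |
| 5% | 0 | 5.7 | 2.9% | 2.7% |
| 5% | 5% | 5.4 | 3.4% | 3.0% |
| 10% | 0 | 5.4 | 3.4% | 3.0% |
| 10% | 10% | 4.8 | 4.6% | 3.5% |
| 20% | 0 | 4.8 | 4.7% | 3.5% |
| 20% | 20% | 3.6 | 7.8% | 4.8% |

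Worked line (10% both ways, 6-point margin): pE' = 0.12×0.9 + 0.06×0.1 = 0.114 and pT' = 0.06×0.9 + 0.12×0.1 = 0.066. The difference is 0.048 and SE = 0.0443. Φ(0.012/0.0443 − 1.96) = Φ(−1.69) = 4.6%.

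**Step 4: planning assumption true (ESD 3%, TAMIS 6%, 6-point margin).** The same dilution now works against ESD. Power falls from 80.1% to 77.3% with 5% cross-over both ways, 74.4% with 10% and 68.0% with 20%.

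**Step 5: relax the risk assumption.** Take 10% ESD-to-TAMIS cross-over at the 6-point boundary.

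- If rescued patients keep a 12% risk, the ESD arm stays at 12% and the false-claim rate stays at 2.5%.
- If they are harder lesions with, say, an 18% risk (an assumption) and the other 90% have 12%, the ESD arm is 0.9×12% + 0.1×18% = 12.6%, and the rate falls to about 1.8%.

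**The case against.** Five points count on the other side.

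1. The word used is primarily, which leaves room for further analyses. A journal article commonly leaves analysis sets to the full protocol or analysis plan, neither of which is shown. This stands as far as it goes: a reader might infer that intention-to-treat is the only analysis planned, and the documents do not support that. What they do fix is the basis of the primary conclusion, together with a permitted route into the comparator. The point rests on those two stated choices and not on a missing analysis.

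2. Intention-to-treat answers a legitimate question: how patients fare when ESD is tried first and rescue is available. The Abstract and Discussion speak of guiding the choice of approach, which fits that reading. It is a good reason to keep intention-to-treat as primary. It does not settle the matter, because the hypothesis, aim and test are worded for the procedures.

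3. Cross-over may be rare. Operators need at least 25 prior procedures and 10 of the latest 15 with an R0 resection and no complications, an expert panel approves each lesion, and cross-over needs the receiving specialist's agreement. At 2% both ways the rate is 2.8%, which is negligible.

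4. It is tempting to say that the more often ESD fails and is rescued, the more alike the arms must look. Step 5 shows that this is not generally true: the effect disappears or reverses if failures are the high-risk lesions.

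5. A per-protocol set of completed procedures removes ESD's own failures. If overall ESD risk is 12% and the 10% who fail have 18% (assumed), completers have (12 − 1.8)/0.9 = 11.3%, so per-protocol can flatter ESD. This stands. It is why per-protocol should not replace intention-to-treat, and why a second analysis that counts failures is needed.

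**Conclusion.** The concern holds in a limited form. Resting the non-inferiority conclusion primarily on intention-to-treat, with cross-over to the comparator permitted, can modestly raise the false-claim rate. Three conditions are needed: ESD truly worse, cross-over not rare, and crossed patients taking on roughly the risk of the treatment received. Under them the 2.5% becomes about 2.9% to 3.4% for 5% to 10% ESD-to-TAMIS cross-over and about 4.6% for 10% both ways at the 6-point margin, or about 3.5% for 10% both ways at the 3-point margin.

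The size is hypothetical because no cross-over rate is given, and the sign is not guaranteed. If ESD is as good as planned, the cost is power (80.1% to about 74% at 10% both ways), not a false claim. A reader might infer that the trial is biased towards declaring non-inferiority whatever happens, or that intention-to-treat is the wrong primary analysis. The documents support neither. What they support is that intention-to-treat should not carry a claim about the procedure unaided.

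**What to change.** Keep intention-to-treat as the primary analysis and pre-specify, before outcome data are seen, two analyses with the same margin and confidence interval:

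- (a) A per-protocol analysis of patients in whom the allocated procedure was received and completed and the endpoint assessed, with a statement that this set is selective because it drops failed procedures.
- (b) A sensitivity analysis that counts cross-over for procedural failure as an unfavourable outcome of the allocated arm. Rescue by the comparator cannot flatter this result.

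Claim non-inferiority of the ESD procedure only if the intention-to-treat upper limit is below the margin and the per-protocol result agrees. Report (b) beside them, with the number and direction of cross-overs per arm. Adding a condition to the claim cannot raise the false-claim rate.

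The cost is wording, two analyses and some power, since the per-protocol set is smaller and both conditions must be met. The cross-over rule is left as written. The 6-point and 3-point margins must be reconciled separately before any of these analyses can be specified.
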